## 2. Material and Methods

This piece of research is a single center prospective controlled trial conducted at the Regional Hospital of Melilla (Spain), which will facilitate voluntary participant recruitment and the supervised CTR program component.

This research involves the departments of Cardiology, Rehabilitation, Physiotherapy, and Research at the University of Granada. All CTR staff will receive training on how to integrate the intervention training. As this study runs parallel to clinical practice, all medical management, including medication prescription, will be at the discretion of the treating physician. All changes will be documented and considered during analysis. 

This research uses the guidelines on Standards for Quality Improvement and Excellence in Reporting (SQUIRE) [18] and will be carried out in accordance with CONSORT (Consolidated Standards of Reporting Trials) criteria [19]. A Standard Protocol Items Recommendations for Interventional Trials (SPIRIT) checklist is provided as Supplementary File S1, and the flow diagram for the study protocols is included as Figure 1.

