### 2.1. Patients

The trial includes adults with a diagnosis of low-risk CVD with class I heart failure according to the NYHA (New York Heart Association) functional assessment criteria (24), diagnosed by the Cardiology and Rehabilitation team of the Hospital of Melilla. Patients must live in Melilla during the intervention phase, have mobile technology with an internet connection at home (including one of the following devices: desktop personal computer, laptop, tablet, or smartphone), and be able to access email or instant messaging frequently and reliably. Patients who suffered non-mild cardiac events prior to the first contact with this research, those whose pathologies are not classified as CVD, and those subjects who are not in full cognitive capacity that allows them to use new technology tools will be excluded. Patients will be excluded if they have any absolute or relative contraindications to exercise testing as per the American Heart Association guidelines [20]. Inclusion and exclusion criteria is show in Table 1.

In order to generate sufficient data for the development of this research, a sample size of (*n* = 30) patients will be recruited. The primary aims of this sample size determination is to evaluate whether the proposed intervention is feasible, safe, and effective. A larger randomized controlled trial that would have adequate power could be designed based on what was learned in this study. The strategies to achieve an adequate inclusion of participants that reach the target sample size include the multidisciplinary collaboration of the team from the Regional Hospital of Melilla (Cardiology Department, Head of the Rehabilitation Service and the Physiotherapy team). The collaborators were informed about the characteristics of the study in personal interviews and presentation. We ensured that the recruitment of patients has a socio-demographic diversity in relation to their social origin, gender, ethnicity, and education adapted to the particularities of the reference population. For the development of this research, an intentional non-probabilistic type of sampling will be used for the convenience of the study, due to the characteristics of the subjects. This trial has the approval of the Andalucía Ethics Committee with HIP version 17112020.

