### 2.4. Data Collection Procedure, Monitoring, and Management

Once participants have been informed and agree to participate in the study, data will be collected for statistical analysis. This data collection will take place in the period February–June 2021. Initial assessment (Pre) and final 8-week assessment (Post) will be carried out by the research team with the cardiology, rehabilitation, and physiotherapy departments. The data will be aggregated to a research database created for this purpose and managed by the principal’s research using exportable data tables for statistical analysis. 

The research is designed in 4 stages, as presented in Figure 1 in a study design flow diagram:

Stage 1 includes 2 different processes: firstly the identification of candidates, the provision of prior information and the signing of informed consent in the event that the subjects agree to participate. Secondly, the assessments by the cardiology department with ergometry and biochemistry test at (T0-Pre). This stage ends with the referral to the rehabilitation department.

Stage 2 includes: the assessments by the rehabilitation department with quality of life, functional capacity outcomes, and comorbidity index added to previous clinical information. At this stage, the Modified Borg Scale Education is offered to participants to assess their level of fatigue during exercise. A personalized CTR program is proposed according to the Physiotherapy Department. This stage ends with the referral to the Physiotherapy department and CTR staff.

Stage 3 includes: 8 weeks CTR program with the supervision of the Physiotherapy Department and the CTR staff. An initial 1-to-1 session is offered with technology management and patient education. Daily follow up sessions include the progression, barriers of use, and adverse event records. CTR team will updates programs according to participant’s feedback and rehabilitation supervision.

Stage 4 includes: Final assessments and evaluation (T1-Post). At this stage, cardiology, rehabilitation, physiotherapy and principal research are compiled into the results of clinical and self-reported outcomes after 8 weeks CTR program including: biochemistry, ergometry, quality of life, and functional capacity. At this stage, satisfaction and usefulness, economic data safety, and adherence records will be added to research data’s for statistical analysis

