## 3. Results

Enrollment began in February 2021. First study results will be reported in the middle of 2021. Recruitment is currently underway. The recruitment goal is 30 cardiac rehabilitation patients. Data collection is anticipated to be complete by July 2021.

If the results confirm beneficial effects in biochemical, cardiac function, quality of live, and functional capacity, the effectiveness of the intervention will be proven in patients with heart failure. The successful delivery of the intervention, the absence of significant adverse effects, and the user satisfaction will demonstrate the feasibility of these interventions in cardiac patients.

The results of this study will determine if a larger-scale intervention is feasible. Further, this pilot study will be the first to examine the effect of CTR intervention on patients in a cardiac rehabilitation setting in Melilla (Spain). The results of this study will provide differences compared to previous research: first of all, its implementation in the autonomous city of Melilla (located on the African continent with particular demographic characteristics); secondly the use of the innovative CTR platform based on the App Physiotec; thirdly, the collection of outcomes that combine clinical, self-reported and economic data and lastly, automated treatment adherence registry.

This study will add more evidence in support of the use of CTR program as an effective tool in new cardiac rehabilitation programs.

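### The choice among eligible patients is left to staff discretion, so adherence, satisfaction and feasibility may be overestimated; consecutive invitation with a short log would limit this

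*Protocol article*

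**What the plan says.** All references are to the protocol article.

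- **Selection.** Section 2.1 says that "an intentional non-probabilistic type of sampling will be used for the convenience of the study, due to the characteristics of the subjects". No order of approach or other rule is attached to this.
- **Diversity.** The sentence before it says: "We ensured that the recruitment of patients has a socio-demographic diversity in relation to their social origin, gender, ethnicity, and education". It adds that this is adapted to the reference population. Section 3 says "Recruitment is currently underway".
- **Who recruits.** Section 2.1 relies on the cardiology, rehabilitation and physiotherapy teams to reach 30 patients. In Section 2.4, Stage 1 covers "the identification of candidates, the provision of prior information and the signing of informed consent" together with the cardiology assessments. Stage 2 has rehabilitation assess the patient and a personalized program proposed according to physiotherapy. Stage 3 has physiotherapy and the telerehabilitation staff supervise the eight weeks.
- **Who can enter.** Section 2 describes a hospital setting "which will facilitate voluntary participant recruitment and the supervised CTR program component". Section 2.1 and Table 1 require a device and home internet, and Section 2.1 requires patients to "be able to access email or instant messaging frequently and reliably".
- **Use of the results.** Section 1 makes adherence and feasibility main aims alongside efficacy. Section 3 says: "The results of this study will determine if a larger-scale intervention is feasible". It also says that successful delivery, absence of significant adverse effects and user satisfaction will demonstrate feasibility in cardiac patients, without limiting this to patients like those enrolled.

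**The concern.** Two patients who meet every criterion need not have the same chance of being approached, because the plan leaves that choice open. The program asks for at least one session a day, largely self-performed, for eight weeks (Section 2.2). Adherence and satisfaction therefore plausibly depend on motivation. If discretion happens to favour motivated patients, the sample will look better than the eligible population.

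This matters because these results are not side measures here. They are to decide whether a larger study goes ahead, and Section 2.1 says a larger randomized trial could be designed from what is learned. Planning figures for uptake and session completion taken from a favourably selected sample would be too optimistic. The fault lies in who enters, so it has to be limited at recruitment; it cannot be repaired in the analysis.

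**Working it through.** The plan gives no figure for this point, so there is nothing to reproduce. The check sets the statements side by side and then illustrates the possible size.

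**1. Does any rule limit selection?** Section 2.1 gives eligibility criteria, then names convenience and the patients' characteristics as the basis for sampling. Those characteristics are not specified. Section 2.4 lists identification and consent without an order of approach. As written, selection among eligible patients is discretionary.

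**2. Do recruiters also deliver?** In part. Rehabilitation and physiotherapy appear both among the recruiting teams (Section 2.1) and in planning or supervising the program (Section 2.4, Stages 2 and 3). Cardiology appears in recruitment and assessment only. Stage 1 does not say which team identifies candidates.

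**3. Is the diversity statement supported?** No quota, stratum or target is described, and recruitment was still open. Purposive sampling can be a means to diversity, so the gap is the missing mechanism; the two sentences do not conflict.

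**4. Why the denominator matters.** The article's own background (Section 1) shows it: 44.8% of patients were advised to attend rehabilitation and 81.4% of those attended. As 0.448 × 0.814 = 0.365, uptake is 81.4% among those advised but 36.5% among all patients.

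**5. Possible size (assumed inputs).** Let *p* be the true proportion of eligible patients who would adhere. Let *k* be the chance of enrolment for an adherer relative to a non-adherer. Neither is in the documents. The plan records adherence as number of sessions, so treating it as yes/no is a simplification. The expected proportion in the sample is

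observed = *kp* / (*kp* + 1 − *p*)

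For *p* = 0.60 and *k* = 2: 1.20 / (1.20 + 0.40) = 0.75, which is 15 points too high. For *p* = 0.50 and *k* = 3: 1.50 / (1.50 + 0.50) = 0.75, which is 25 points too high.

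| True *p* | *k* = 1 | *k* = 1.5 | *k* = 2 | *k* = 3 |
|---|---|---|---|---|
| 50% | 50.0% (0) | 60.0% (+10.0) | 66.7% (+16.7) | 75.0% (+25.0) |
| 60% | 60.0% (0) | 69.2% (+9.2) | 75.0% (+15.0) | 81.8% (+21.8) |
| 70% | 70.0% (0) | 77.8% (+7.8) | 82.4% (+12.4) | 87.5% (+17.5) |
| 80% | 80.0% (0) | 85.7% (+5.7) | 88.9% (+8.9) | 92.3% (+12.3) |

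**6. Compared with sampling error.** With 30 patients, the exact (Clopper-Pearson) 95% interval is 50.6% to 85.3% for 21/30 and 61.4% to 92.3% for 24/30. For 21/30 the half-width is (85.3 − 50.6)/2 ≈ 17 points. A selection effect in the middle of the table would be of similar size, and the interval makes no allowance for it.

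**The case against.** The strongest reply is that openly disclosed non-probability sampling of volunteers is usual in a 30-patient, single-center pilot, and that it mainly limits generalizability. Sections 2.1 and 4 defer adequate power and comparison groups to later trials. Screening logs and recruitment procedures are details that an article may leave to the full protocol. Much of this stands. The absence of a log from the article is not a fault in itself. The point rests on the sampling method that the article does state, and on Section 3 drawing a conclusion wider than that method supports.

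Three stronger readings are tempting, and the documents do not support them:

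- A reader might infer that staff hand-pick likely adherers, so that the results are biased upward. Nothing says that motivation, skill with technology or expected adherence guides the choice. Access to technology is an explicit criterion and so defines the target population; it is not hidden selection among eligible patients.
- A reader might infer that every recruiting team has a stake in the program. Cardiology has no delivery role in Section 2.4, so the overlap is partial.
- A reader might infer that the diversity sentence contradicts intentional sampling. It does not. An argument from its past tense is also weak, because the article mixes tenses throughout.

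Finally, participation is voluntary and enrolment had begun. Consecutive invitation therefore cannot remove self-selection or be applied to patients already enrolled. That limits the remedy but does not remove the reason for it.

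**Conclusion.** The concern holds in a limited form. The plan fixes a discretionary method of selection for a study whose main aims include adherence and feasibility, and some of the staff involved in recruitment also plan or supervise the program. Overestimation is possible and its direction plausible. Its existence and size cannot be established: the 0 to 25 point range depends entirely on the assumed *k* of 1 to 3 and *p* of 50% to 80%, and with *k* = 1 there is no bias. The diversity statement is unsupported as worded. The feasibility conclusion for cardiac patients in general goes beyond what such a sample can show. The change is worth making because it is cheap and the problem would be invisible in the data afterwards.

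**What to change.** 1. **Section 2.1, sampling.** For the remaining enrolment, replace convenience selection with consecutive invitation: every patient who meets the stated criteria is invited in order of presentation until 30 are enrolled. Flag patients enrolled before the change.
2. **Log.** Record those eligible, invited, declining and not invited, with age, sex, education and the reason. Report uptake (enrolled divided by eligible) as a feasibility result.
3. **Section 2.1, diversity.** Replace the statement that diversity was ensured with a planned comparison of enrolled patients against the log. Social origin and ethnicity can be claimed only if they are logged too.
4. **Section 3.** Limit the feasibility conclusion to patients like those enrolled.

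The cost is a change of protocol wording and a short log at one hospital, with no additional patients or study assessments. Observed adherence may be lower. Enrolment may take longer, by an amount that cannot be estimated because no flow of eligible patients is given, and Section 2.4 sets data collection for February to June 2021. Self-selection by volunteers remains, but the log would make refusals visible.

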### 2.2. Intervention

Participants are assigned to the cardiac telerehabilitation group to receive an initial assessment. The CTR group receives a personalized 8-week exercise program through a mHealth application that allows health professionals to generate videos, images, and parameters of each exercise, as well as send them by email, instant messaging, and follow up on patients. In this study, we use the Physiotec exercise prescription app as it allows us to create personalized CTR programs according to particular clinical case and follow their progress. The CTR program describes the exercises to be performed, the number of repetitions according to the level of training and the criteria for progression. The CTR program includes aerobic exercise at 60–85% of the maximum heart rate (HR) reached in the ergometry test. As patients are taking β-blocker drugs, they will never reach their maximum HR. Patients will be instructed in the use of the Modified Borg Scale to assess their level of fatigue while performing the CTR program. Exercises customized to each participant should be performed between values 4–6 on this scale (out of a maximum of 10).

The type of exercise can be continuous or intervallic (load or HR controlled):

Continuous Exercise: After an initial warm-up period of 5–10 min, the patient is brought into a phase where he or she remains at a HR or resistance previously determined by the intervention team.

Interval Exercise: After an initial warm-up period, an exercise is started which alternates load peaks with lower intensity ones.

All patient training sessions should end with a return to the initial baseline situation (relaxation phase) of similar duration to the warm-up phase 5–10 min.

Typical CTR training session: -Control of basal constants (by the patient): HR, blood pressure, weight, blood sugar…-Permanent monitoring during the whole CTR session (patient must understand and follow the modified Borg scale as well as to use activity bracelets, pulse meters, or other monitoring instruments)-Exercise session:
∘Initial warm-up: 5–10 min (follow-up the video exercises provided through the CTR tool).∘Aerobic training: 35–45 min (follow up the video exercises provided through the CTR tool)∘Return to calm, relaxation-cooling: 5–10 min (follow up of the video exercises provided through the CTR tool)∘Recording of incidents and patient feedback in the CTR tool. Patient/physiotherapist feedback

Patients are initially supervised by the research team who will conduct 1-to-1 training sessions to ensure proper execution of the exercises and encourage patient adherence. Patients are instructed to perform self-training by following the video exercises through the CTR program. At the beginning of the study, advice is given on general care, in physical activity and issues concerning drug intake.

Patients are advised to refrain from any other specific training during the intervention period. Any deviations from the adherence and practice of the CTR program are recorded daily, noting any adverse incidents.

The TR group receives a personalized program for 8 weeks, including at least one session per day and is done through a web and mobile application. The telerehabilitation application allows health professionals to create personalized exercise programs, hold video conferences with patients, generate videos, images and parameters of each exercise, as well as send them by email and follow up patients through the mobile application.

### 2.3. Outcome Measures

Affiliation Data and Socio-Demographic Questionnaire: including age, gender, location, and other socio-demographic variables.

#### 2.3.1. Main Explanatory Variable

-Biochemical outcomes: obtained by blood analysis performed at the Hospital of Melilla including the following measures: red blood cell levels, glucose, creatine kinase (CK), triglycerides, cholesterol, high-density lipoprotein cholesterol (HDL-C), low-density cholesterol (LDL-C), and glycosylated hemoglobin (HbA1c).-Cardiac function: obtained by performing an ergometry test at the Hospital of Melilla, including the following measurements: metabolic equivalent (MET), resting heart rate (HRrest), maximum heart rate (HRmax), and final heart rate (HRfinal), rating of perception of exertion scale (RPE), systolic blood pressure (SBP), diastolic blood pressure (DBP).-Quality of life: obtained through the completion of self-reported questionnaires with the advice of the research team. The assessment of health-related quality of life will be assessed by the following two questionnaires: SF-12 and EuroQoL-5d. The SF-12 questionnaire is the short version of the SF-36, containing twelve questions from the SF-36. [21]. The SF-12 is an appropriate instrument of choice and is a practical alternative for measuring the general health status of the population [22]. The SF-12 questionnaire assesses eight dimensions of health-related quality of life: physical function, physical role, bodily pain, general health, vitality, social function, emotional role, and mental health [21]. Two sum scores are also obtained for the physical health component and the mental health component of the person. Thus, the sum index of the physical and mental component corresponds to the overall idea of general health. The EuroQoL-5D Questionnaire (EQ-5D) contains a descriptive system of one’s health status measured in five dimensions (mobility, self-care, activities of daily living, pain, and anxiety/depression) [23]. The EQ-5D has a visual analog scale (VAS) that assesses health status “on the present day” with scores ranging from 0 (worst imaginable health status) to 100 (best imaginable health status). The EQ-5D questionnaire provides information on the level of the problem (no problem, somewhat/moderate problem or severe problem) [24]. It has been shown to be a tool with an acceptable validity, with an estimated mean of 0.87 [25].-Functional capacity: For the assessment of functional capacity we will use the Duke Activity Status Index (DASI). It is an assessment tool used to evaluate the functional capacity of patients with cardiovascular disease, such as coronary artery disease, myocardial infarction, and heart failure. It is a validated instrument and its Spanish version is available [26,27]. The original version include 12 questions on aspects of physical function related to activities of daily living. It allows a calculation of functional capacity reporting results in ml of O2/kg/minute with good correlation with peak VO2, and in turn can be compared with the METs [28].

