The Charlson Comorbidity Index (CCI) will be included in the demographic, anamnesis and medical history data [33]. CCI is a system for evaluating life expectancy at ten years, depending on the age at which it is evaluated and the subject’s comorbidities. 

We will try to ensure that the sample data are similar at baseline and there are no significant differences in demographic, medical and other outcomes. The homogeneity of the sample will be analyzed and normality tests will be performed. An outline of the primary (4 dimensions) and secondary outcomes (3 dimensions) is shown at Table 2:

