## Figures and Tables

**Figure 1 ijerph-18-04038-f001:**
[figure not shown]
Study design. Abbreviations CVD, cardiovascular disease; CTR, cardio-telerehabilitation.

**Table 1 ijerph-18-04038-t001:** Inclusion and exclusion criteria.

Inclusions Criteria	Exclusions Criteria
Adult over 18 Years old	Cognitive ability not suitable for the use of technologic tools.
Diagnosis: Ischemic heart disease in New York Heart Association (NYHA) functional class I-II with preserved global systolic function or in intermediate range (LVEF > 40%) after revascularized acute coronary syndrome.	
Lives in Melilla during the research period.	Absolute or relative contraindications to exercise testing
To have mobile technology with an internet connection at home (including one of the following devices: desktop personal computer, laptop, tablet, or smartphone)	
Ability and knowledge to access email or instant messaging	

Abbreviations LVEF, Left ventricular ejection Fraction.

**Table 2 ijerph-18-04038-t002:** Primary and secondary outcomes.

	Definition	Type
Primary Outcomes		
Biochemical	Hematies Level, Glucose, Creatine Kinase (CK), Triglycerides, Total Cholesterol, High Density Lipoprotein Cholesterol (HDL-C), Low Density Lipoprotein Cholesterol (LDL-C), Glycated Hemoglobin (HbA1c)	Clinical
Cardiac Function	Metabolic Equivalent (MET), Resting Heart Rate (RHR), Maximum Heart Rate (HRmax), Final Heart Rate (FHR), Rating Scale for Perceived Exertion (RPE), Systolic Blood Pressure (SBP), Diastolic Blood Pressure (DBP)	Clinical
Quality of Life	SF-12, EQ-5D	Self-Reported
Functional Capacity	Duke Activity Status Index (DASI)	Self-Reported
Secondary Outcomes		
Feasibility, Satisfaction and Usefulness	Telemedicine Satisfaction and usefulness Questionaire (TSUQ)	Self-Reported
Cost-Effectiveness	Direct Costs/Indirect Costs	€/Self-Reported
Adherence and Safety	Nº of sessions completed and adverse events record	Automatized App record

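### The research team that trains the patients also advises them on the primary quality-of-life questionnaires, an avoidable risk of response bias in an uncontrolled before/after comparison

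*Protocol article*

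**What the plan says.** All references are to the protocol article.

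- **How quality of life is collected.** Section 2.3.1 says that the SF-12 and EQ-5D data are "obtained through the completion of self-reported questionnaires with the advice of the research team". The sentence sets no limit on that advice. The DASI entry in the same section mentions no advice.
- **Who trains.** Section 2.2: "Patients are initially supervised by the research team who will conduct 1-to-1 training sessions". These sessions are also meant to encourage adherence.
- **Who assesses.** Section 2.4 says that the initial and the 8-week assessments "will be carried out by the research team with the cardiology, rehabilitation, and physiotherapy departments".
- **How the stages divide the work.** Stage 2 has "the assessments by the rehabilitation department with quality of life, functional capacity outcomes, and comorbidity index added to previous clinical information". Stage 3 is the "8 weeks CTR program with the supervision of the Physiotherapy Department and the CTR staff". At Stage 4, cardiology, rehabilitation, physiotherapy and the principal research side all contribute to the clinical and self-reported results. Satisfaction (TSUQ) enters only at this stage.
- **Status of the outcomes.** Section 2.3.2: "An outline of the primary (4 dimensions) and secondary outcomes (3 dimensions) is shown at Table 2". Table 2 labels two of the four primary dimensions as self-reported: quality of life and functional capacity (DASI).
- **Analysis and conclusion.** Section 2.5 compares outcomes before and after the 8-week programme at the 0.05 level. Section 2.2 describes assignment to the telerehabilitation group only. Section 3 says that confirmed benefit would prove effectiveness.

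**The concern.** A self-reported score is open to influence from whoever is present and helping when it is filled in. Here the helper is named as the research team, which also delivers part of the intervention and has an interest in the result. Patients know that they had the programme, and no independent assessor is described.

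In a trial with a concurrent control arm handled in the same way, some of this influence would cancel. Here it would cancel only if it were equal at both visits, and nothing in the text secures that. Any part that is larger after the programme goes straight into the estimated change and cannot be told apart from benefit. At stake is one primary dimension, and possibly a second, in a study that would present a significant improvement as proof.

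**Working it through.** **Step 1. Which outcomes does the advice cover?**

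| Instrument | Role | Label in Table 2 | Advice documented? | Measured at |
|---|---|---|---|---|
| SF-12, EQ-5D | Primary | Self-reported | Yes (2.3.1) | T0 and T1 |
| DASI | Primary | Self-reported | No; team involvement follows only from the general sentence in 2.4 | T0 and T1 |
| TSUQ | Secondary | Self-reported | No | T1 only |

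The documented exposure is 1 of 4 primary dimensions. With DASI it could be 2 of 4, by inference.

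**Step 2. Is it the same team?** Sections 2.2, 2.3.1 and 2.4 use the same name for those who train, advise and assess. The stage description in 2.4 is finer: rehabilitation takes quality of life and DASI at baseline, physiotherapy and programme staff supervise the 8 weeks, and several departments contribute at the end. The shared name is documented. That the same individuals do all three is not.

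**Step 3. Are T0 and T1 collected alike?** At T0 these questionnaires belong to Stage 2, before the patient is referred to physiotherapy and programme staff. At T1, physiotherapy is among the contributing departments. No passage states that one administration procedure applies at both visits. The settings may therefore differ, but the text does not say who is with the patient at either visit.

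**Step 4. What could a small shift do?** The plan gives no figure for response bias, and the sample of 30 comes without an effect size, SD or power, so there is no figure of the plan's own to reproduce. The following is for scale only.

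Inputs: n = 30 (2.1); significance level 0.05 (2.5), taken as two-sided. Assumptions: a paired t-test, complete data, no true effect, and a shift b in units of the SD of the pre/post change.

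Smallest observed mean change that reaches significance:

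t(0.975; 29)/√30 = 2.045/5.477 = 0.373 SD.

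Rejection probability: P(|T| > 2.045), where T is noncentral t with 29 df and noncentrality b√30.

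| Assumed shift b | Noncentrality | Two-sided rejection | Of which towards improvement |
|---|---|---|---|
| 0 | 0 | 5.0% | 2.5% |
| 0.1 | 0.548 | 8.3% | 7.6% |
| 0.2 | 1.095 | 18.5% | 18.4% |
| 0.3 | 1.643 | 35.5% | 35.5% |

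These rates are per score. They depend only on b, whatever its source.

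**The case against.** The strongest reply has five parts.

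1. **Advice may be neutral.** It may mean no more than explaining how to fill in the form, given alike at both visits. Such help need not move the change score. This stands as far as size and direction go: the documents fix neither. It does not remove the risk, because the article states the advice as part of the procedure and leaves it open.

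2. **Administration rules belong in the full protocol.** A condensed article may leave out such detail, and omission alone would be no finding. The point here rests on what the article does state: advice from the team that also trains.

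3. **The stronger reading is inference.** A reader might infer that bias is built into two of the four primary dimensions and into the satisfaction score, with patients answering at T1 beside the staff who coached them for 8 weeks. The documents do not support this. Advice is written for SF-12 and EQ-5D only. Who administers DASI and TSUQ is not specified beyond the general assessment sentence. The stages divide the work between departments, and much of the programme is self-training from videos. TSUQ is a T1 measure, so a pre/post shift cannot apply to it.

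4. **The rejection rates are not specific to this defect.** Regression to the mean, natural recovery or any other drift of the same size would give the same figures. This stands. They show how little an uncontrolled comparison tolerates, and they do not measure the effect of advice.

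5. **Changing the mode now could do harm.** Section 3 says that recruitment is under way. Patients with an assisted T0 and an unaided T1 would carry a mode change inside their own comparison. Leaving out assisted forms could also selectively remove patients who need help, in a sample of 30 for which section 2.1 seeks diversity in education. Both points stand and shape the fix.

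**Conclusion.** The point holds in a limited form. The article has a primary self-reported outcome completed with open-ended advice from a team of the same name as the one that trains the patients and takes part in both assessments. In an uncontrolled before/after comparison that section 3 would read as proof, this is an avoidable risk of prompting or social-desirability bias towards improvement after the programme.

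It is a risk and not a demonstrated bias. It is documented for quality of life, one of four primary dimensions, and is only possible for DASI. The illustrative rates of about 8%, 19% and 36% per score rest on assumed shifts of 0.1, 0.2 and 0.3 SD, a paired two-sided test, 30 complete pairs and no true effect.

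The point does not invalidate the trial, and correcting it leaves the sample size unchanged. It is worth correcting because it touches a primary outcome and costs little.

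**What to change.** In section 2.3.1, replace the phrase on the research team's advice with wording such as:

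> Patients complete SF-12, EQ-5D and DASI themselves, by the same procedure at T0 and T1 and before contact with programme staff at that visit. Help is limited to reading items aloud or to technical access, without comment on the answers. Each assisted form is flagged. TSUQ is self-completed in the same way, at T1 only.

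Then add:

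- **Patients already enrolled.** Record the mode of completion at both visits. Where T0 was assisted, avoid a change of mode within the patient at T1.
- **Analysis.** Keep all patients in the main analysis. Report results without assisted forms as a sensitivity analysis only.

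Paper forms are enough. The exercise application is not described as carrying questionnaires, so the wording should not rely on it.

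**Cost:** a short change of text, one field on the form and some care over patients already enrolled, with no extra staff or visits. A few more items may be skipped. Unaided completion reduces courtesy bias but does not remove it, because patients know that they received the programme.
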